## 2. Materials and Methods

### 2.1. Design

This is a prospective, observational investigation designed to identify factors associated with treatment response and prognosis in a clinical anxiety group. The study population comprises two groups: individuals with anxiety disorders and a healthy control group. The anxiety group will complete assessments at baseline, 4 months, and 12 months, whereas the control group will undergo a single baseline assessment. The overall follow-up period is 12 months, with participant enrollment and data collection planned from 2024 through 2029.

Although no structured therapeutic intervention is administered as part of the research protocol, participants in the clinical anxiety group may receive naturalistic treatment-as-usual, including pharmacological or psychotherapeutic interventions, as determined by their treating clinicians. Accordingly, the study does not involve randomization, allocation concealment, or blinding procedures. The overall design and temporal structure of the study assessments are illustrated in Figure 1.

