### 2.4. Discontinuation and Dropout Criteria

Participants may be discontinued from the study under the following circumstances: emergence of adverse events or significant exacerbation of symptoms, voluntary withdrawal of consent, development of serious medical or psychiatric conditions that preclude continued participation, or the principal investigator’s judgment that termination is necessary for the participant’s well-being.

Dropout is defined as non-compliance with the study protocol, including missing scheduled assessments or failing to attend follow-up visits within the designated visit window (±15 days from the scheduled date).

In cases of either discontinuation or dropout, the principal investigator will inform the participant of the rationale and any necessary actions to be taken. The research team will take all reasonable steps to ensure participant safety, including offering follow-up care or appropriate referrals. With the participant’s consent, data collected prior to withdrawal may be retained and used for analysis.

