### 2.5. Observational Parameters and Clinical and Laboratory Assessments

Participants in the clinical anxiety group will complete assessments at four timepoints: baseline and 2, 6, and 12 months. The healthy control group will be assessed at baseline and 12 months. The timepoints were chosen to efficiently assess symptom improvement at 2 months, check for relapse at 12 months for the clinical anxiety group, and confirm continued health for the healthy control group. These intervals also minimize participant burden while ensuring comprehensive data collection over the course of a year. Assessments will include clinical interviews, standardized self-report questionnaires, computerized neurocognitive testing, VR-based behavioral evaluations, physiological recordings (EEG and ECG), and multimodal brain imaging (structural, functional, and diffusion MRI).

Given the 12-month follow-up period and the multimodal nature of the assessments, challenges related to participant burden and attrition are anticipated. To mitigate these risks, the study incorporates flexible scheduling, abbreviated interim assessments at selected follow-up visits, and the option for remote administration of questionnaires where appropriate. These strategies are intended to support participant retention and ensure data completeness while maintaining methodological rigor.

Figure 2 summarizes the timing and scope of these assessments across both groups. At each timepoint, specific instruments have been selected to capture transdiagnostic symptom dimensions and neurobehavioral mechanisms aligned with the RDoC framework—particularly domains related to Negative Valence Systems, Cognitive Systems, and Arousal/Regulatory Systems.

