### 2.6. Outcomes and Operational Definitions

The primary outcome of this study is treatment response, operationally defined as a clinically meaningful reduction in panic symptom severity. Responders are defined as participants who achieve a ≥40% decrease in the total score of the PDSS from baseline to each follow-up assessment (2, 6, and 12 months), while participants not meeting this criterion are classified as non-responders.

This threshold was selected based on prior evidence indicating that a 35–45% decrease on disorder-specific anxiety scales corresponds to clinically meaningful improvement and early treatment benefit [30,31]. The 40% criterion also provides adequate sensitivity for detecting within-subject improvement across multiple timepoints in longitudinal designs.

To ensure conceptual coherence with the study’s transdiagnostic framework, additional analyses will examine changes in the GAD-7, DASS-21 Anxiety subscale, and LSAS as secondary outcomes, and the consistency of responder classification across these measures will be evaluated. This multi-metric approach retains sensitivity to panic-specific reactivity while enabling comparability with broader anxiety-disorder literature.

These operational definitions allow for both categorical classification (responder vs. non-responder) and continuous modeling of symptom change, facilitating the integration of clinical, behavioral, physiological, and neuroimaging predictors across the 12-month follow-up.

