### 2.7. Sample Size and Power Considerations

This study is designed to identify predictive biomarkers of treatment response through multimodal data modeling in a prospective, observational framework. Since the primary goal is to develop prediction models rather than to test predefined hypotheses, traditional power calculations based on inferential statistics are not directly applicable.

For the cross-sectional comparison between the clinical anxiety group and the healthy control group, a medium effect size (Cohen’s d = 0.5) was assumed based on prior neuroimaging meta-analyses [32]. This yielded a minimum required sample size of 36 participants per group to achieve 80% power at a two-sided α = 0.05. Accounting for a 10% attrition rate, the control group target was set at 40 participants.

Sample size planning for predictive modeling was based on guidelines by Riley et al. [33], which recommend ensuring a sufficient number of events per predictor parameter to reduce the risk of model overfitting. Although the dataset includes numerous raw variables across clinical, behavioral, physiological, and neuroimaging domains, only a subset (~20 variables) will be used in each model following feature selection procedures. Assuming a non-response rate of 25% (the reported remission rate of 38–75% at 6 months) [34,35], at least 80 non-responders would be required to ensure four events per predictor. Accordingly, the clinical anxiety group was targeted at 145 participants to allow for a 20% dropout rate and ensure sufficient statistical power for model development.

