### 3.3. Predictive Modeling of Treatment Response

The primary objective is to develop machine-learning models that predict treatment response (≥40% PDSS reduction at 2, 6, and 12 months). Binary (responder vs. non-responder) and three-group models (healthy control, responder, non-responder) will be evaluated. Predictor features will include sociodemographic and psychiatric-history variables, clinical and psychometric scores, VR-derived behavioral indices, EEG/ECG features, 3D skeletal tracing, and neuroimaging markers. In most models, age and sex will be treated as basic covariates given their known influence on neural and behavioral measures. Lifestyle variables (e.g., education, smoking, alcohol use) and treatment-related clinical variables (medication use and psychotherapy) will be systematically recorded and incorporated either as covariates to adjust for treatment effects or as candidate predictive features, depending on the specific modeling objective and analytic context.

Predictor inclusion and feature reduction will be guided by a combination of theoretical relevance and empirical criteria. Candidate variables will undergo an initial screening based on prior literature and clinical interpretability. Dimensionality will then be reduced using data-driven feature-selection procedures, such as penalized regression methods (e.g., LASSO) or feature-importance-based ranking, with the number of retained features determined by model performance and stability rather than a predefined target. Variables exhibiting substantial multicollinearity (e.g., variance inflation factor > 5), redundancy, or consistently low contribution across cross-validation folds may be excluded prior to model fitting.

All features will be standardized, and missing values handled using multiple imputations by chained equations or similar robust approaches. Depending on data characteristics, dimensionality-reduction techniques (e.g., principal component analysis) may be applied before model fitting.

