### 3.4. Statistical Considerations

All analyses will be exploratory and hypothesis-generating. Normality of data distributions will be verified using the Shapiro–Wilk test and residual diagnostics. If assumptions for parametric tests are violated, appropriate transformations or non-parametric alternatives will be employed. Potential covariates (age, sex, medication status, treatment type) will be included as needed. Missing data will be handled using multiple imputation or complete-case analysis, depending on the extent and mechanism of missingness.

To ensure generalizability, model interpretability, and prevention of overfitting, we will report confidence intervals, cross-validation performance variability, and model calibration statistics where applicable. Robustness checks (e.g., bootstrapping with 1000 iterations) will be performed to confirm model stability. All analyses will be implemented in R (version 4.3.1 or later) and Python (version 3.10 or later). The analysis code will be managed using a version-controlled repository (Git), and the final software environment, including package versions, will be documented to ensure reproducibility.

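### The primary responder label spans three visits with no stated reading and no primary visit, and neither it nor the dropout rule says how a missing or late PDSS score is classified

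*Protocol article*

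**What the plan says.** Section 2.6 makes treatment response the primary outcome. A responder has a fall of at least 40% in PDSS total score "from baseline to each follow-up assessment (2, 6, and 12 months), while participants not meeting this criterion are classified as non-responders". The modelling target in section 3.3 is to "predict treatment response (≥40% PDSS reduction at 2, 6, and 12 months", again with no visit singled out.

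Other sections point to different times:

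- Section 2.5 says the visits were chosen to "efficiently assess symptom improvement at 2 months, check for relapse at 12 months for the clinical anxiety group".
- Section 2.7 sizes the study on 6-month figures: "Assuming a non-response rate of 25% (the reported remission rate of 38–75% at 6 months".
- Section 2.1 gives another schedule: "The anxiety group will complete assessments at baseline, 4 months, and 12 months".

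On missing data, section 3.4 states: "Missing data will be handled using multiple imputation or complete-case analysis, depending on the extent and mechanism of missingness". It does not mention the responder label. The imputation sentence in section 3.3 appears alongside the standardisation of features.

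Section 2.4 counts as dropout missing scheduled assessments or "failing to attend follow-up visits within the designated visit window (±15 days from the scheduled date". It then says that data collected before withdrawal may be kept with consent, and is silent on scores obtained later.

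**The concern.** Every binary model in the study is trained on this label, so it has to be computable in one way from a participant's scores. As written it is not, for two reasons.

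First, the reference to each of three follow-ups can mean one sustained label or three separate labels. A sustained label does not match a 25% non-response assumption taken from a single time point. Three separate labels, none primary and each open to several algorithms, leave the headline result to be chosen after the data are seen.

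Second, the non-responder class is defined as everyone who does not meet the criterion, with no not-evaluable category. A participant with no follow-up PDSS could be a non-responder under section 2.6, imputed under one option of section 3.4, or excluded under the other. If such participants enter as non-responders, a model of non-response partly predicts non-attendance. The dropout rule in section 2.4 widens the problem, because a participant who attends late may have a usable score that the protocol neither admits nor rules out.

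**Working it through.** **Inputs from section 2.7:** clinical group 145, dropout 20%, non-response 25%, cited remission 38–75% at 6 months. Taking 1 minus remission, the cited range corresponds to 25–62% without remission.

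**The plan's own figure.** 145 × (1 − 0.20) = 116 completers, and 116 × 0.25 = 29 non-responders. Section 2.7 asks for 80. That shortfall is a separate matter; only the 145, 20% and 25% are used below.

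**1. All-three reading against per-visit reading.** The documents give neither a per-visit response rate nor a correlation between visits. I assume 75% response at each visit (the complement of the planned 25%) and a trivariate normal latent variable with equal correlation ρ. Then P(response at all three) = P(Z₁, Z₂, Z₃ all below the 75th percentile), and non-response is its complement.

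| ρ | Response at all three | Non-response |
|---|---|---|
| 0.4 | 0.51 | 49% |
| 0.6 | 0.56 | 44% |
| 0.8 | 0.62 | 38% |

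Under a per-visit label, non-response stays at 25% by assumption.

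**2. Dropouts in the non-responder class, on the literal reading of section 2.6.** Dropouts = 145 × 0.20 = 29. Share = 29 / (29 + 116 × completer non-response rate).

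| Completer non-response | Observed non-responders | Dropout share |
|---|---|---|
| 25% | 29.0 | 50% |
| 38% | 44.1 | 40% |
| 50% | 58.0 | 33% |
| 62% | 71.9 | 29% |

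The two results do not stack. At the 38–49% non-response of the all-three rule, 116 completers give about 44–57 non-responders and the dropout share is about 40–34%, not 50%.

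**3. How easily the dropout rule is triggered.** With independent on-time attendance a at each of three visits (assumed), P(at least one breach) = 1 − a³.

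- a = 0.90: 1 − 0.729 = 27%.
- a = 0.93: 1 − 0.804 = 20%, which matches the planned rate.

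The documents give no attendance figure, so this shows only how sensitive the rule is.

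**The case against.** A reader might infer that half of the non-responders will be dropouts. The documents do not support that. Section 2.6 does not mention missing scores, and a percentage change cannot be evaluated without a follow-up value. Section 3.4 offers multiple imputation or complete-case analysis, and under neither is a missing score automatically non-response. Section 2.7 enlarges the sample to allow for dropout, which treats dropouts as lost rather than as events. The 50% is therefore an upper figure that needs both the literal wording and the 25% rate. What stands is that the sections are not tied together.

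A reader might also infer that late attenders' scores will be discarded, or that dropout will exceed 20%. Section 2.4 permits earlier data to be kept but does not say that later data are excluded. The 27% comes from an assumed attendance rate, and 93% gives about the planned figure. Section 2.5 also plans flexible scheduling and remote questionnaires to limit attrition.

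Finally, section 3.4 calls all analyses exploratory, comparing algorithms is ordinary model development, and a separate label per visit is a natural reading of section 3.3. This weakens any complaint framed as formal multiplicity. It does not settle the label: section 2.6 names a primary outcome, section 2.7 sizes the study on a single rate for it, and neither the reading nor the visit is stated.

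**Conclusion.** The point holds in a limited form. The primary label has more than one reading and no primary visit, and sections 2.1, 2.5 and 2.7 point to different times. The choice of reading moves non-response from 25% to about 38–49%, assuming 75% response at each visit and latent correlations of 0.4–0.8.

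Sections 2.4, 2.6 and 3.4 can assign different labels to the same participant whose score is missing or late. The possible contamination of the non-responder class is 29–50%, conditional on reading section 2.6 literally and on completer non-response of 62–25%.

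It does not follow that 6 months must be the primary visit. The 6-month figure in section 2.7 is remission rather than a 40% PDSS fall, and section 2.5 links improvement to 2 months. The case for changing the text before outcomes are seen rests mainly on the undefined label and visit; the dropout shares are secondary.

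**What to change.** - **Sections 2.6 and 3.3:** state that response is defined per visit and name one primary visit before outcomes are seen. Six months would align with the source used for sizing, but the sponsor should choose and justify the visit. Make response at the other visits, and sustained response, secondary. Reconcile the schedule in section 2.1 with the 2-, 6- and 12-month visits used elsewhere.
- **Sections 2.6 and 3.4:** state that a missing PDSS is missing and is not non-response. Handle it by multiple imputation, with a complete-case sensitivity analysis.
- **Section 2.4:** record a missed or late visit as a deviation at that visit, keep the participant in follow-up, and use a late score with its actual date. Reserve dropout for withdrawal or loss of contact.

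The cost is protocol wording. Two visit labels become secondary, and the timing of scores varies slightly more.

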### 2.7. Sample Size and Power Considerations

This study is designed to identify predictive biomarkers of treatment response through multimodal data modeling in a prospective, observational framework. Since the primary goal is to develop prediction models rather than to test predefined hypotheses, traditional power calculations based on inferential statistics are not directly applicable.

For the cross-sectional comparison between the clinical anxiety group and the healthy control group, a medium effect size (Cohen’s d = 0.5) was assumed based on prior neuroimaging meta-analyses [32]. This yielded a minimum required sample size of 36 participants per group to achieve 80% power at a two-sided α = 0.05. Accounting for a 10% attrition rate, the control group target was set at 40 participants.

Sample size planning for predictive modeling was based on guidelines by Riley et al. [33], which recommend ensuring a sufficient number of events per predictor parameter to reduce the risk of model overfitting. Although the dataset includes numerous raw variables across clinical, behavioral, physiological, and neuroimaging domains, only a subset (~20 variables) will be used in each model following feature selection procedures. Assuming a non-response rate of 25% (the reported remission rate of 38–75% at 6 months) [34,35], at least 80 non-responders would be required to ensure four events per predictor. Accordingly, the clinical anxiety group was targeted at 145 participants to allow for a 20% dropout rate and ensure sufficient statistical power for model development.

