### 3.2. Brain MRI Analysis

Preprocessing for MRI data will use standardized pipelines: fMRIPrep v24.0 for T1 and resting-state fMRI (anatomical segmentation, motion correction, spatial normalization, and smoothing at 6 mm full-width half maximum), and QSIPrep v0.21 for DWI (eddy-current correction, bias-field correction, and tensor fitting).

Structural MRI, diffusion-weighted imaging (DWI), and resting-state fMRI will be analyzed to comprehensively characterize brain structure, white matter integrity, and intrinsic functional organization associated with anxiety and treatment response. Structural MRI will yield cortical thickness and gray matter volume measures; DWI will provide white matter microstructural indices, including fractional anisotropy and mean diffusivity; and resting-state fMRI will be used to derive functional connectivity, amplitude of low-frequency fluctuations, and regional homogeneity as candidate neurobiological features for group comparisons and predictive modeling.

Group-level comparisons will be performed between (i) healthy controls and anxiety participants and (ii) responders and non-responders using general linear models with age and sex as covariates. Multiple comparisons will be adjusted using the false discovery rate. Significant neural indices will be further examined as candidate predictive features in multimodal modeling.

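### The stated 36 per group does not give 80% power for d = 0.5 (64 per group are needed); the planned 145 versus 40 comes close, and the text should say so

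*Protocol article*

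**What the plan says.** Section 2.7 first says that conventional power calculations do not directly apply to the main aim, which is building prediction models. It then gives one such calculation. "For the cross-sectional comparison between the clinical anxiety group and the healthy control group", "a medium effect size (Cohen’s d = 0.5) was assumed", and this is said to give a "minimum required sample size of 36 participants per group to achieve 80% power" at two-sided alpha 0.05. After a 10% allowance for attrition, "the control group target was set at 40 participants".

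The patient group is sized separately in the same section, on events per predictor and a 20% dropout allowance, at 145. The Abstract confirms 145 patients and 40 controls.

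Section 3.2 sets out the imaging analysis of this comparison: general linear models with age and sex as covariates, and "Multiple comparisons will be adjusted using the false discovery rate". Section 3.4 labels all analyses exploratory.

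**The concern.** All the inputs of a standard two-sample calculation are printed: effect size, alpha, sidedness, power and two independent groups of equal size. The result printed beside them is a little over half of what they require. This is not detail left to a fuller document, since no further detail would make 36 follow from those inputs.

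Two things depend on it. The control target is derived directly from 36. And this is the only numerical power in the article, so a reader who wants to know what the patient-control comparison can detect has only this sentence to go on. Section 3.2 also carries significant neural indices from the group comparisons forward as candidate predictors, so the sensitivity of that step matters to the modelling.

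**Working it through.** **Inputs.** From Section 2.7: d = 0.5, two-sided alpha 0.05, power 80%, two independent groups, 36 per group, 10% attrition. From the Abstract: 145 patients and 40 controls.

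**1. Trying to reproduce 36 per group.**
- Normal approximation: n = 2(z₀.₉₇₅ + z₀.₈₀)²/d² = 2(1.960 + 0.842)²/0.25 = 62.8, so 63 per group.
- Exact noncentral t: n = 63.8, so 64 per group.

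The figure of 36 is not reproduced.

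**2. What 36 per group delivers.**
- Noncentrality d√(n/2) = 0.5 × √18 = 2.12 on 70 degrees of freedom.
- Power is 55.3% (56.4% by the normal approximation).
- The effect detectable with 80% power is d = 0.67.

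**3. Whether another assumption explains 36.**

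| Variant (d = 0.5, 80% power) | n |
|---|---|
| One-sided alpha 0.05 | 51 per group |
| Wilcoxon test (efficiency 3/π) | 67 per group |
| Two-sided alpha 0.10 | 51 per group |
| Two-sided alpha 0.20 | 37 per group |
| Paired or one-sample t-test | 34 pairs |

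Only the last two come near 36. One contradicts the stated alpha, the other the comparison of two independent groups. Covariate adjustment would reduce 64 to 36 only if the covariates had a multiple correlation of √(1 − 36/63.77) = 0.66 with the outcome. The article states no such correlation for age and sex.

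**4. The attrition step.** 36/(1 − 0.10) = 40. This step is correct, so the control target carries over the error in 36 and adds none of its own. On the same equal-group reasoning, 64 would have become 64/0.9 = 71.1, so 72.

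**5. Power of the planned design.** Noncentrality is d√(n₁n₂/(n₁ + n₂)), for a single unadjusted test at two-sided 0.05.
- 145 versus 40: 0.5 × √(5800/185) = 2.80; power 79.5%.
- 145 versus 36: 0.5 × √(5220/181) = 2.69; power 76.1%.
- With 145 patients, 80% is first reached at 41 controls.

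**6. Direction of the multiplicity effect.** The false discovery rate has no fixed per-test threshold. It depends on the number of tests and the share of true effects, and the article gives neither. For assumed per-test thresholds, power at 145 versus 40 is:

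| Assumed threshold | Power |
|---|---|
| 0.01 | 58% |
| 0.005 | 49% |
| 0.001 | 30% |

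The range is wide. Only the direction is secure: power is below the unadjusted figure.

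**The case against.** The strongest reply is that the 55% belongs to a design nobody will run. The patient group has 145 members for other reasons, and with 40 controls the unadjusted power is 79.5%, in effect the claimed 80%. This stands, and it sets the size of the point. It does not rescue the sentence: Section 2.7 claims 80% for 36 in each group and never appeals to the larger patient group.

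It can also be said that the comparison is secondary to prediction modelling, that Section 2.7 limits the role of power calculations, and that Section 3.4 calls everything exploratory. This lowers the severity. It does not make a stated calculation correct, and an enrolment target was set from it.

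Several stronger readings are tempting and not supported:
- **That the comparison will run at 55% power, or that 72 controls must be recruited.** Both assume equal groups, which are not planned.
- **That a null imaging result will be taken as evidence of no difference.** The article draws no such inference and plans no equivalence claim.
- **That quoting nominal alpha is itself an error because Section 3.2 adjusts.** Giving power for one unadjusted test is acceptable if it is labelled as such. No single adjusted power can be derived from the article.
- **That the patient dropout of 20% should be applied as well.** It arises during follow-up and does not bear on a baseline comparison.
- **That the 10% control allowance has no place.** The article is not consistent here: Section 2.1 gives controls one baseline visit, while Sections 2.5 and 7 bring them back at 12 months. For the baseline comparison the allowance makes sense only as controls without usable data.

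**Conclusion.** The statement in Section 2.7 is wrong as written. For d = 0.5 at two-sided 0.05, 80% power takes 64 per group, and 36 per group gives about 55%. The control target of 40 was derived from the wrong number.

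The severity is moderate. The planned unequal groups largely restore the power, to about 80% with 40 controls or 76% with 36, for one unadjusted test. These figures assume a two-sample t-test with equal variances and no gain from the age and sex covariates. Power after the false discovery rate adjustment is lower by an amount that the article does not allow one to fix.

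**What to change.** In Section 2.7, delete the statement that 36 per group suffice and replace it with the power of the planned allocation, for example:

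*With 145 patients and 40 controls, power is about 80% (79.5%) to detect d = 0.5 in a single unadjusted two-sided test at 0.05, or about 76% if 36 controls are evaluable. Power is lower after the false discovery rate adjustment described in Section 3.2.*

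Describe the 10% allowance, for the baseline comparison, as controls without evaluable data. Do not print one specific power after adjustment. If an illustration is wanted, show a range of per-test thresholds labelled as assumptions, as in step 6 of the working.

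The cost is two sentences and no change in enrolment. The control target of 40 can stay, justified by the power it gives alongside 145 patients rather than by 36/0.9.

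### The prediction sample size counts about 20 predictors after feature selection, while the analysis selects on the outcome with no fixed number retained, so the events-per-predictor rule does not give the protection claimed

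*Protocol article*

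**What the plan says.** Section 2.7 follows a guideline whose aim it describes as "ensuring a sufficient number of events per predictor parameter to reduce the risk of model overfitting". It concedes that "the dataset includes numerous raw variables across clinical, behavioral, physiological, and neuroimaging domains", but counts only what is left at the end: "only a subset (~20 variables) will be used in each model following feature selection procedures". From this it concludes that "at least 80 non-responders would be required to ensure four events per predictor". It then states that "the clinical anxiety group was targeted at 145 participants to allow for a 20% dropout rate", and that this number gives enough statistical power to develop the model.

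Section 3.3 describes the primary analysis. Candidates come from sociodemographic, clinical, psychometric, VR, EEG/ECG, skeletal-tracking and neuroimaging data. They are first screened on literature and interpretability, then reduced by data-driven methods such as LASSO or importance ranking, "with the number of retained features determined by model performance and stability rather than a predefined target". Performance is typically to be assessed by k-fold or nested cross-validation.

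Section 3.2 adds a further route into the model. Neural indices found significant in group comparisons, one of which is responders versus non-responders, are carried forward as candidate predictors.

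**The concern.** There are two faults, and both lie in what the text states.

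First, the wrong quantity is counted. Outcome-driven selection uses the data on every candidate it tries, including those it discards. Twenty survivors of a search carry the optimism of the whole search. An events-per-parameter ratio worked out on the survivors leaves that out.

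Second, the two sections disagree. Section 2.7 needs about 20 predictors for its arithmetic, and Section 3.3 says that no such target exists. Nothing in the analysis holds the model to the number on which the sample size rests.

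At stake is the adequacy claim in 2.7. A reader would take it that the sample guards against overfitting at the stated ratio, when the ratio that the design delivers is unknown. If selection is also done once on all the data before cross-validation, which the wording permits, the reported performance itself would be biased upwards.

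**Working it through.** **1. The plan's own figure.** Inputs from Section 2.7: about 20 predictors and 4 events per predictor. 20 × 4 = 80 non-responders, which reproduces the stated requirement. It is correct only for a model offered 20 parameters in total.

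**2. Events the sample delivers.** Section 2.7 gives 145 enrolled, 20% dropout and 25% non-response. 145 × 0.80 = 116 completers, and 116 × 0.25 = 29 non-responders. Reaching 80 at 25% would need 80 / 0.25 = 320 completers, or 320 / 0.80 = 400 enrolled. This shortfall is a separate error. The present point is tested at 80 events as well, to show that it does not depend on the shortfall.

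**3. Events per candidate parameter.** Ratio = events / candidates. The documents give no candidate count, so the counts below are assumptions.

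| Candidates | With 80 events | With 29 events |
|---|---|---|
| 20 | 4.0 | 1.45 |
| 50 | 1.6 | 0.58 |
| 100 | 0.8 | 0.29 |
| 200 | 0.4 | 0.15 |

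The ratio of four holds only in the first row, with 80 events.

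**4. Illustration with no true signal.** Predictors are independent standard-normal noise, so the true AUC is 0.50. The 20 with the largest difference between outcome classes are kept and a near-unpenalised logistic model is fitted, with 200 runs per cell. Cross-validation is 5-fold. Selection is done either once on all the data (outside) or anew in each training set (inside). Repeat runs differ by about 0.01.

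| Patients / events | Candidates | Apparent AUC | CV AUC, selection outside | CV AUC, selection inside |
|---|---|---|---|---|
| 320 / 80 | 20 (no selection) | 0.66 | 0.50 | 0.50 |
| 320 / 80 | 100 | 0.78 | about 0.69 | 0.50 |
| 320 / 80 | 500 | 0.85 | about 0.78 | about 0.50 |
| 116 / 29 | 20 (no selection) | 0.77 | about 0.50 | about 0.50 |
| 116 / 29 | 100 | 0.92 | about 0.75 | about 0.50 |
| 116 / 29 | 500 | 0.98 | about 0.86 | about 0.50 |

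All rows fit 20 predictors. Within each sample size only the candidate pool changes, and the optimism grows with it. The 20 retained is therefore not the number that governs overfitting, and supplying the full 80 events does not change that.

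**The case against.** The strongest reply is that the plan has other safeguards. Section 3.3 screens on literature and interpretability before any data-driven step, allows principal components before fitting, ties retention to performance and stability, and permits removal of collinear, redundant or weak variables. LASSO shrinks coefficients. Section 3.4 promises calibration statistics, performance variability and bootstrap checks, and calls all analyses exploratory.

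Much of this stands, and it limits the point in four ways.

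- A reader might infer that the number of features is unlimited. The text says only that there is no predefined number.
- A reader might infer that the pool is far larger than 20. That is plausible from the list of modalities, but the raw variables in 2.7 are counted before the literature screening, and the number left after it is never given.
- A reader might infer that the study will report inflated AUCs. Apparent AUC is not the plan's metric, and cross-validation with selection inside the folds shows no inflation. The plan neither commits to nor rules out that arrangement: nested cross-validation is one of two options, and the 3.2 screening is described apart from the folds.
- A reader might infer that the selected markers must prove unstable. The simulation does not show this, and its simple ranking plus logistic refit does not stand for every algorithm listed in 3.3.

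What does not stand is the idea that these safeguards rescue 2.7. Proper validation makes the performance estimate honest; it does not make a post-selection count the right input to the rule. The exploratory label also sits beside an explicit claim of adequate power.

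**Conclusion.** The point holds in this form: Section 2.7 applies an events-per-predictor rule to variables counted after selection, Section 3.3 does not hold the analysis to that count, and the claim that the sample size gives adequate power for model development is therefore unsupported. This would remain true with 80 non-responders.

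The conclusion rests on the wording of 2.7, 3.2 and 3.3 and on the general property of outcome-driven selection, not on the simulated values. Those show direction and rough size under assumed pools of 100 to 500 independent noise candidates; correlated features, a smaller screened pool or stronger penalisation would give different figures. If the screened pool held only about 20 parameters, the count would be right, but the document does not say so. The matter should be corrected. It does not undermine the study's exploratory aim.

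**What to change.** 1. In Section 2.7, state how many candidate parameters enter any step that uses the outcome, and give the events per candidate parameter that the sample is expected to deliver. Withdraw the claim that 145 patients give adequate power for a model of about 20 selected features.
2. Reconcile 2.7 with 3.3 in one of two ways. Either fix the candidate set for the primary model by reduction that is blind to the outcome (a literature-based list, or a set number of component scores per modality), or drop the figure of 20 from the sample-size argument.
3. In Sections 3.2 to 3.4, require every outcome-based selection step, including the screening of neural indices on responder status, to be repeated inside each cross-validation fold and each bootstrap sample.

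This needs no new patients or data. The cost is a less favourable sample-size statement and more computation. With the first option in step 2, the primary model may also miss a feature outside the fixed set, which a wider search could still examine. A particular cap, such as the 7 parameters obtained from 29 / 4 = 7.25, is not required; it would trade heavily against the multimodal objective.
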